# HATRIC: a study of *Pelargonium sidoides* root extract EPs®7630 (Kaloba®) for the treatment of acute cough due to lower respiratory tract infection in adults—study protocol for a double blind, placebo-controlled randomised feasibility trial

**DOI:** 10.1186/s40814-019-0478-6

**Published:** 2019-07-31

**Keywords:** Feasibility, Herbal, Double-blind randomised, Retention, Variance, Stratification, Lower respiratory tract, Acute bronchitis, Cluster randomised

## Abstract

**Background:**

Acute lower respiratory tract infection is a common acute infection managed in primary care. The current dominant management strategy in the UK is antibiotics, despite widespread publicity regarding antimicrobial resistance and evidence that the small benefits of antibiotics do not outweigh the harms. There is a need to address the rising problem of antibiotic resistance by providing credible alternative strategies, which reduce symptom burden. There is sufficient evidence to recommend the use of *Pelargonium sidoides* root extract in order to warrant undertaking an independent clinical trial.

We propose a feasibility study to demonstrate our ability to recruit and retain patients and conduct a placebo-controlled trial of *Pelargonium sidoides* extract EPs®7630 in lower respiratory tract infection where pneumonia is not suspected. Both the tablet and liquid formulations will be included.

**Methods:**

The HATRIC trial is a double-blind randomised placebo-controlled feasibility study aiming to determine the potential to conduct a fully powered trial of *Pelargonium sidoides* root extract as an alternative to the inappropriate use of antibiotics for acute bronchitis in UK primary care.

Primary care sites will be equally randomised to one of two formulation groups (tablet or liquid preparation). Additionally, within each site, patients will be evenly randomised to active or placebo treatment. Antibiotic consumption will be monitored during the trial, but the use of a delayed prescription strategy is encouraged. The target sample size for this study is 160 patients overall or 40 per arm, recruited from approximately 20 primary care sites. The analysis will be descriptive focusing on estimation with no formal comparison of groups taking place.

**Discussion:**

If this trial demonstrates the feasibility of recruitment and delivery, we will seek funding for a fully powered placebo-controlled trial of *Pelargonium sidoides* root extract for the treatment of lower respiratory tract infections in primary care.

**Trial registration:**

HATRIC was registered on the ISRCTN registry (ISRCTN17672884) on 16 August 2018.

## Background

Acute non-pneumonic lower respiratory tract infection (LRTI)/acute bronchitis is a common acute infection managed in primary care. A systematic review of the use of antibiotics for acute bronchitis suggested modest benefits; however, the authors suggested that any modest benefits that accrued were matched by harm from side effects from antibiotics [1]. In the largest of the contributing studies [2], no subgroups were identified who derived clinically relevant benefit from antibiotics [3]. Avoidance of unnecessary antibiotic prescriptions is one of the key components of the UK’s national action plan on tackling antimicrobial resistance [4, 5].

Antibiotics are still widely and inappropriately prescribed for acute bronchitis in the UK with no sign of substantial reduction despite widespread publicity regarding antimicrobial resistance [6–8]. Various strategies have been proposed in national guidelines including delayed prescribing [9] and wider use of the C-reactive protein (CRP) test [10] but have yet to have substantial impact. The symptoms of acute bronchitis are troublesome, and cough is known to persist for around 3 weeks on average [2, 11]. One alternative approach is to provide symptom relief, which in conjunction with a delayed prescription if effective may substantially reduce antibiotic uptake. The impact of effective alternative treatments for respiratory infections is likely to be in minimising unnecessarily severe or prolonged symptoms and avoiding side effects from unnecessary antibiotics; minimising the long-term public health risks of inappropriate antibiotics and providing a model for different management strategies for other respiratory tract infections (RTIs).

Some potential candidates for symptom relief such as steam inhalation have not been shown to be helpful [12] whilst ibuprofen had no significant benefit [13] and may cause harm [12]. Other potential symptomatic treatments in adults (the expectorant guaifenesin, mucolytics, and antihistamine-decongestant combinations) have not been shown to have consistent benefit in a recently updated Cochrane systematic review [14].

In a systematic review of herbal treatments for acute upper respiratory infection and cough, there was supporting evidence for *Andrographis paniculata* and *Pelargonium sidoides* [15]. A Cochrane review updated in 2013 provided supporting evidence for *Pelargonium sidoides* root extract EPs®7630 in acute respiratory infections in both adults and children [16], and although this is suggested for self-care in the latest draft NICE guidance [17], the quality of the evidence was regarded as very low, suggesting the need for more robust research.

*Pelargonium sidoides* root extract EPs®7630 is widely available over the counter in several countries in Europe, Asia, and Central and South America as well as in Australia. A variety of potential mechanisms have been identified for EPs®7630 which provide a rational basis for its use, including moderate antiviral and antibacterial effects and the possession of immune-modulatory capabilities that are mainly mediated by the release of tumour necrosis factor α and nitric oxides, the stimulation of interferon-β, and an increase in natural killer cell activity [18–21]. Moreover, EPs®7630 has been shown to activate human monocytes, induce mitogen-activated protein kinase-dependent pro-inflammatory cytokines in these cells, and specifically modulate their production capacity of mediators that are known to lead to an increase of acute phase protein production in the liver, neutrophil generation in the bone marrow, and the generation of adaptive T-helper 17 and T-helper 22 cells. An improved phagocytosis, oxidative burst, and intracellular killing by human peripheral blood phagocytes as well as an inhibition of group-A streptococci and host epithelia [19, 21] and an increase of stress resistance [22] was also shown. *Pelargonium sidoides* root extract EPs®7630 interferes with replication of seasonal influenza A virus strains (H1N1, H3N2), human coronavirus, RSV, parainfluenza virus, and coxsackie virus, whilst no direct virucidal effect was observed [23]. Exertion of anti-influenza virus activity was also confirmed in an animal model [24]. The data available therefore constitute sufficient evidence to warrant undertaking a high-quality independent clinical trial of this herbal medicine.

We propose a feasibility study to demonstrate our ability to recruit and retain patients with acute bronchitis in a placebo-controlled trial of *Pelargonium sidoides* extract EPs®7630. Furthermore, we propose to include both liquid and tablet formulations and to use a mixed methods approach to critically examine recruitment and retention issues prior to proceeding with a fully powered trial.

## Methods/design

The HATRIC (Herbal Alternative Treatment (Pelargonium) for Lower Respiratory Tract Infections with Cough in adults) trial (ISRCTN17672884; sponsor reference number: 24375) is a double-blind, randomised placebo-controlled feasibility study, with general practitioner (GP) practices cluster-randomised to give liquid or tablet preparation, and within each practice, eligible patients randomised to *Pelargonium sidoides* root extract EPs®7630 or placebo.

A qualitative study, HATRIC-Q (IRAS project ID: 233467; sponsor reference number: 29921), will also be undertaken with patients, including both those who agreed and those who declined to take part in HATRIC, and clinicians. We will explore their experiences of taking part in the trial and obtain their feedback on trial procedures, as well as their views on the implementation of a delayed antibiotic approach and the use of herbal medicine for the treatment of lower respiratory tract infection. This qualitative sub-study is described fully in a separate protocol.

### Objectives

The aim of this study is to determine the feasibility of conducting a fully powered trial of *Pelargonium sidoides* root extract as an alternative to inappropriate use of antibiotics for lower respiratory tract infections in UK primary care. Specific feasibility objectives are detailed below (see Table 1).

**Table 1 Tab1:** Feasibility objectives and endpoints for the HATRIC trial

Feasibility objective	Endpoint used to evaluate
Eligibility: number of patients included and number excluded (+ reasons) from the trial	On site screening logs
Recruitment: ability to recruit patients into the intervention from those attending primary care	On site enrolment records—monthly rate/site adjusted for site list size
Randomisation: willingness to be randomised	Proportion of eligible patients recruited
Retention: across the duration of the intervention and return of a fully completed diary	Quantitative data from enrolment Withdrawal rate from study Completion of outcome measures
Intervention compliance	Diary data and returned medication
Patient preference for liquid/tablet formulation	Diary data Returned medication Recruitment data
Establish the frequency of collecting EQ5D questionnaire and identifying the key resources associated with the intervention and potential influence on service usage Establish methods of data collection for the health economics analysis	Development of health economic protocol and collection of outcome data EQ-5D-5L questionnaire and case note review
Acceptability of the patient diaries, patients’ willingness to complete them, and the importance of telephone/text contact	Quantitative data collection—percentage of patients returning completed diaries
Success of delayed antibiotic strategy	Diary data on day antibiotics commenced
Need for stratification by antibiotic strategy in main study	Proportion allocated to immediate and delayed antibiotic strategy
To inform sample size for future trials	Rate of outcome measures in the control group
Quality of life measurements and resource use	Identify the key resource items to be collected and how often to collect EQ-5D-5L in the full trial

### Study participants and enrolment

The inclusion and exclusion criteria for the HATRIC trial are listed in Table 2. Up to twenty health centres in the Wessex region of the UK will identify eligible patients and will invite them to participate in the trial.

**Table 2 Tab2:** Eligibility criteria for the HATRIC trial

Inclusion criteria	
1. Adults 18 years and over	
2. Presenting with an acute cough (≤ 21 days’ duration) as their main symptom	
3. Presenting with symptoms localising to the lower tract (e.g. sputum, chest pain, dyspnoea, wheeze), for which an infective diagnosis is judged very likely	
4. Willing and able to give written informed consent	
Exclusion criteria	
1. Suspected pneumonia (i.e. complicated lower respiratory tract infection) on the basis of focal chest signs (focal crepitations, bronchial breathing) and systemic features (severe breathlessness, high fever, vomiting, severe diarrhoea)	
2. Signs of severity which may warrant hospital admission (e.g. SpO2 < 91% [30, 31], Systolic BP < 90 mmHg, Heart rate > 130)	
3. Exacerbation of COPD	
4. Serious chronic disorders where immediate antibiotics are needed (e.g. cystic fibrosis, valvular heart disease)	
5. Unable to give informed consent or complete trial paperwork (including the patient diary)	
6. Difficulty reading and understanding English and therefore unable to give informed consent or complete the trial paperwork (including the patient diary)	
7. Known or suspected pregnancy	
8. Women at risk of pregnancy (i.e. not on effective contraception—combined oral contraceptive pill, an intrauterine hormonal device, subcutaneous hormonal implant, or hormonal contraceptive injections)	
9. Currently breast-feeding	
10. Known immunodeficiency state or chemotherapy	
11. Currently taking oral steroids	
12. Using a *Pelargonium sidoides*/Kaloba® preparation and unwilling or unable to discontinue for the study period	
13. Hypersensitivity to *Pelargonium sidoides* preparations or to the Kaloba brand	
14. Increased tendency to bleeding or is taking coagulation-inhibiting drugs (e.g. warfarin)	
15. Severe hepatic and renal diseases (Chronic Kidney Disease Stage 4, GFR < 30), as no adequate data are available in these areas	
16. Rare hereditary problems of galactose intolerance, the Lapp lactase deficiency, or glucose-galactose malabsorption (tablet formulation only)	
17. Previously entered the HATRIC trial	
18. Recruited to another interventional trial in the previous 6 weeks	

They will be given a full explanation of the trial, an information leaflet, and allowed sufficient time to decide whether to participate and ask any questions they may have. Only then will written informed patient consent be obtained by the recruiting GP or nurse or by appropriately trained healthcare assistants or clinical trials assistants. The right of the patient to refuse to participate without giving reasons will be respected. After the patient has entered the trial, the clinician remains free to give alternative treatment to that specified in the protocol at any stage if he/she feels it is in the patient’s best interest, but the reasons for doing so will be recorded. In these cases, the patients will remain within the trial for the purposes of follow-up and data analysis. All patients will be free to withdraw at any time from the protocol treatment without giving reasons and without prejudicing further treatment.

All eligible patients including those who decline to be involved in the trial will be invited to consider being interviewed for the HATRIC-Q study. Those entering the trial will be asked to provide consent for their contact details to be shared with the qualitative researcher. Those who decline participation in the HATRIC trial will be given an invitation letter for HATRIC-Q, and if interested, they will contact the qualitative researcher directly.

Women of childbearing potential will be required to use one of the most effective contraceptive methods (combined oral contraceptive pill, hormonal intrauterine device, hormonal contraceptive injection, or subcutaneous hormonal implant) to enter the trial. There are no safety data available for pregnant women, and therefore, the manufacturing authorisation in Germany for the Kaloba® preparation specifies that it must not be taken by women who are pregnant or breastfeeding.

Screen failures will be documented in the screening log maintained at each participating site, together with reasons for exclusion.

Patients who are not eligible or who declined to take part in the HATRIC trial will be given, by the GP, nurse, or research assistant, a letter with a reply slip inviting them to participate in HATRIC-Q.

### Randomisation

Participating primary care sites will be randomised to either tablet or liquid preparation in a 1:1 allocation ratio. GPs and patients will know whether they are receiving tablets or liquid, as this cannot be blinded.

In each site, patients who meet the eligibility criteria for the study and for whom written informed consent can be obtained will be individually randomised to either the active or the placebo treatment of either the tablet or the liquid form depending on the site allocation. This individual randomisation will be block randomised (with varying block size) in a 1:1 allocation ratio of placebo to active treatment, and no stratification factors will be used.

The treatment packs will be sent to sites in sets of four, and each patient will be allocated the next available sequentially numbered patient pack at their site. The doctor or nurse allocating the patient pack and the patient will not know to which arm they have been randomised (placebo or EPs®7630). The patient pack will contain either *Pelargonium sidoides* root extract EPs®7630 in liquid or tablet form OR matching placebo.

### Trial procedures

#### Baseline

At the initial visit the patient’s relevant past medical history, baseline symptoms, and vital signs will be recorded.

Patient’s baseline symptoms—The severity of the listed symptoms will be scored according to the following system: 0 = no problem, 1 = very little problem, 2 = slight problem, 3 = moderate problem, 4 = bad problem, 5 = very bad problem, and 6 = as bad as it could be. The symptoms captured will be cough, phlegm, shortness of breath, wheeze, blocked or runny nose, chest pain, muscle aches, headaches, disturbed sleep, general feeling of being unwell, fever, and interference with normal activities.

Patient’s vital signs—The following patient vital signs will be recorded: blood pressure; heart rate; temperature; oxygen saturation levels (Sats); C-reactive protein (CRP), if measured; and presence of wheeze or crackles in the chest.

As part of the baseline data capture, patients will also fill in the first section of the patient diary which contains questions about sociodemographic factors, such as their occupation, employment, and ethnicity; smoking; relevant medical history; present illness; and expectations about antibiotic treatment.

Patients will receive a £5 shopping voucher on entering the trial and a second £5 voucher when they have returned a fully completed diary or have completed a symptom diary by recall over the telephone as a thank you for participating. Contact details will be collected from all patients to enable follow-up phone calls to be made and shopping vouchers to be sent by the research team at the Southampton Clinical Trials Unit (SCTU).

#### Follow-up

##### Patient symptom diary

Patients will complete daily diary data for up to 28 days after presentation. They will be asked to stop completing the diary 2 days after complete resolution of symptoms. The collection of diary scores will not be limited to the time during which study medication is being used, to allow the capture of total symptom duration. The diary has previously been validated and is sensitive to change and internally reliable [25, 26].

Patients will also keep a record of the number of times trial medication has been taken every day and, if applicable, when antibiotics or other treatments for their chest infection were taken. Patients will also be asked questions about resource use for their acute bronchitis, including consultations with healthcare professionals in secondary care, medications purchased, and absences from work.

All patients will complete the EQ-5D-5L questionnaire at baseline (day 1) and day 7, and half of the patients will also be randomly selected to complete the questionnaire at additional time points on day 2 and day 4. This will allow us to assess the acceptability of the frequency in collecting quality of life data.

After recruitment, patients will be contacted after 1–2 days to check for any problems with diary completion. Patients will be contacted again after 14 and 28 days to prompt diary completion and return. In the event of diaries not being returned, a brief telephone interview to collect the key data will be undertaken after 35 days. Patients will also be contacted in the event that a diary is returned incomplete, to obtain missing key data.

Contact with patients at each time point will be made initially by text or email, if the patient has provided a mobile telephone number or an email address, to explain when we will be calling and then by telephone.

Completed diaries will be returned to the Southampton Clinical Trials Unit in a freepost envelope. To improve the return rate of completed diaries, patients who return a fully completed diary or complete a diary by recall will receive a £5 shopping voucher to thank them.

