### Treatments

Primary care sites will be randomised to one of two groups (tablet or liquid preparation), and within each site, patients will be randomised to active or placebo IMP.

This will result in four treatment groups:Liquid *Pelargonium sidoides* root extract EPs®7630—30 drops 3× daily, to be taken 30 min before mealsLiquid placebo—30 drops 3× daily, to be taken 30 min before mealsTablet *Pelargonium sidoides* root extract EPs®7630—one 20 mg tablet 3× daily, to be taken 30 min before mealsTablet placebo—one 20 mg tablet 3× daily, to be taken 30 min before meals

The tablets, liquid, and matching placebos will be provided and packaged ready for distribution to sites by [name] GmbH & Co. KG, Karlsruhe (Germany).

Patients will be asked to take the IMP daily until 2–3 days after symptoms have resolved, but treatment duration should not exceed 2 weeks. If a dose is missed, the patient should not take twice the dose but continue to take their usual dose at the usual time.

The use of the delayed prescription strategy for antibiotics will be encouraged (because it reduces use of antibiotics whilst maintaining patient satisfaction [27]), but clinicians will be able to offer one of three following antibiotic strategies in addition to the randomised intervention:Immediate antibioticsDelayed antibioticsNo antibiotics

No class of antibiotic has been shown to have superior performance to another in the treatment of LRTI/acute bronchitis, and hence, the prescribing physician will prescribe delayed antibiotics according to local guidelines. Patients will be asked to wait 7–10 days before collecting the delayed prescription unless their symptoms show substantial deterioration.

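### The diary can close a day before permitted trial medication ends, and items recorded only in the diary are not followed after it closes

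*Protocol article*

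**What the plan says.** The protocol article gives two stop rules, both counted from resolution of symptoms.

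- **Diary** (Patient symptom diary): "Patients will complete daily diary data for up to 28 days after presentation", followed by "They will be asked to stop completing the diary 2 days after complete resolution of symptoms".
- **Trial medication** (Treatments): "Patients will be asked to take the IMP daily until 2–3 days after symptoms have resolved, but treatment duration should not exceed 2 weeks".

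The diary holds more than symptom scores. "Patients will also keep a record of the number of times trial medication has been taken every day", together with the timing of antibiotics and other treatments. The same section has patients answer questions on resource use, including purchased medication and time off work.

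Several endpoints draw on it. Table 1 (Objectives) gives "Diary data and returned medication" as the source for intervention compliance. It assesses the delayed antibiotic strategy from the diary record of the day antibiotics were started and names no other source. The Health economic analysis plan collects out-of-pocket spending through the diary.

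Other sources exist for some of this. Unused medication and packaging are returned (Accountability). The Notes review covers return visits with a respiratory infection for 28 days and extracts medication, primary care and outpatient visits, and admissions.

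**The concern.** The two rules overlap without matching. A patient may stop both medication and diary two days after resolution, and then nothing is lost. A patient who continues medication for the third day, as the instruction permits, has no open diary day on which to record it. The returned pack will show those doses as used and the diary will not, so two measures of one compliance endpoint can differ for a patient who did everything asked. Whether patients comply well enough to justify a definitive trial is one of the feasibility questions listed in the Statistical analysis plan section.

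A second, separate weakness comes from tying closure to resolution at all. For items whose only named source is the diary, nothing is observed from closure to day 28. A relapse managed at home, or late use of a delayed prescription already issued, would leave no trace there. A late antibiotic start could then be read as no antibiotic use.

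**Working it through.** The article gives no figure on this point to reproduce, so the check compares timelines.

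**Inputs**
- Diary end: 2 days after resolution, at most day 28 (Patient symptom diary).
- Medication end: 2 to 3 days after resolution, at most 2 weeks (Treatments).
- Frequency: three times daily in both formulations; for the tablet, "one 20 mg tablet 3× daily, to be taken 30 min before meals" (Treatments).
- Delayed prescription: patients are asked to wait 7–10 days unless they deteriorate substantially (Treatments).
- Cough lasts around 3 weeks on average (Background).

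**Assumption:** day 1 is presentation and also the first day of medication, so the 2-week limit falls on day 14.

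**Step 1: the medication gap.** Let R be the day of complete resolution.
- Last diary day = min(R + 2, 28)
- Last medication day = min(R + 2, 14) to min(R + 3, 14)
- Largest gap = min(R + 3, 14) − min(R + 2, 28), when positive
- Largest share of treatment days outside the diary = gap / last medication day, which is 1/(R + 3) while R ≤ 11

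| R | Last diary day | Last medication day | Largest gap | Share |
|---|---|---|---|---|
| 1 | 3 | 3–4 | 1 day | 1/4 = 25% |
| 4 | 6 | 6–7 | 1 day | 1/7 = 14% |
| 7 | 9 | 9–10 | 1 day | 1/10 = 10% |
| 11 | 13 | 13–14 | 1 day | 1/14 = 7% |
| 12 | 14 | 14 | 0 | 0 |
| 21 | 23 | 14 | 0 | 0 |

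The gap is 0 or 1 day, so at most 3 × 1 = 3 doses, and it needs R ≤ 11. If the first dose were taken on day 2, the limit would fall on day 15 and the boundary would move by one day, to R ≤ 12.

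**Step 2: the delayed prescription window.** The diary closes before day 7 if R + 2 < 7, so R ≤ 4, and before day 10 if R + 2 < 10, so R ≤ 7. An antibiotic started later in that window by such a patient would fall outside the diary.

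**Step 3: days without observation of diary-only items.** This is 28 − (R + 2):
- R = 5: 28 − 7 = 21 days
- R = 12: 28 − 14 = 14 days
- R = 21: 28 − 23 = 5 days

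**Step 4: which items have another source.**
- Doses: returned medication gives a total.
- Return visits and NHS resource use: notes review.
- Antibiotic start day: the diary is the only source named. The notes review extracts medication, but a prescription already issued need not show when, or whether, it was taken. Table 3 limits concomitant medication recording to serious and specified adverse events.
- Out-of-pocket spending: the diary is the only source named.
- Work absence: asked of the patient under the diary section. The article does not say whether this is a daily item, so it is only possibly affected.

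The day-14 and day-28 contacts are described as prompting diary completion and return. The day-35 recall and the contact for missing data deal with unreturned or incomplete diaries, not with one closed as instructed.

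**The case against.** The strongest reply is that this is a one-day difference in wording in a descriptive feasibility trial with no group comparison. Both rules can be obeyed with no gap, and the 2-week limit on medication removes it for anyone resolving from day 12. At the average cough duration of about 3 weeks, medication ends by day 14 and the diary on about day 23. Ending a daily diary soon after recovery also limits burden, and diary acceptability is itself an objective. Page layout and call scripts belong to documents not shown. All of this stands as a limit on size. It does not make the two stated rules agree.

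Four stronger readings are tempting, and the article does not support them.

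- **Compliance is understated by a known amount.** A reader might calculate recorded over taken doses as 3(R + 2)/3(R + 3): 18/21 = 86% at R = 4 and 36/39 = 92% at R = 10. That assumes expected doses run to R + 3. The article defines no compliance denominator, and with one ending at R + 2 the same patient shows 100%.
- **The mismatch causes the loss of antibiotic and cost data.** It does not. That loss follows from any diary stop tied to resolution and would remain if both rules named the same day.
- **Resource use and relapse go unrecorded.** The notes review covers NHS resource use and return visits, and medical encounters for chest symptoms are recorded as adverse events to day 28. Starting antibiotics after complete resolution would mostly require a relapse, and a new consultation should appear in the notes.
- **The day-7 quality-of-life form is lost for anyone resolved by day 4.** The article states "All patients will complete the EQ-5D-5L questionnaire at baseline (day 1) and day 7" with no exemption for early resolvers, and does not say that the diary stop applies to that form.

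**Conclusion.** The concern holds in a limited form. The Patient symptom diary and Treatments sections do not match: for a patient who resolves by day 11 and takes the longer option, one day of medication (3 doses) falls after the diary has closed, and the two compliance sources can differ by that amount. From day 12 there is no gap. This rests on medication starting on day 1.

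Separately, the diary stop leaves the antibiotic start day, out-of-pocket spending and possibly work absence without a stated source between closure and day 28.

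The article gives no distribution of time to resolution, so the number of patients affected cannot be calculated. The stated average cough duration suggests that the medication gap concerns a minority. This is a minor data-capture inconsistency and does not threaten the trial's main feasibility conclusions.

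**What to change.** Reconcile the Patient symptom diary and Treatments sections without changing the treatment rule. Let daily symptom scoring stop as now stated, but keep the medication record open until the day of the last dose, whenever that is.

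At the day-28 call already scheduled in Table 3, ask all patients, including those who have already returned a diary, about three things since it closed: whether and on which day antibiotics were started, what was bought, and any work absence.

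The cost is one line in the diary instructions and a few questions in an existing call. The downside is slight extra patient burden.
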